### Frequency and plans for auditing trial conduct {23}

Site monitoring and audit will be informed by a risk-based approach, with quality assurance audit undertaken by, or on behalf of, the sponsor if there is cause to do so.

### Plans for communicating important protocol amendments to relevant parties (e.g. trial participants, ethical committees) {25}

Protocol amendments will be subject to review by the research ethics committee and approved changes communicated to trial investigators, the PSC and study site research teams.

### Dissemination plans {31a}

Findings will be published via peer-reviewed journal articles, reporting to the funder, national and international conferences and public, patient, participant and NHS stakeholder groups via written and in person dissemination events. A publication policy and dissemination plan will be agreed by members of the PMG.

## Discussion

This paper describes a protocol for a proposed randomised controlled trial to investigate whether modified therapies can improve quality of life for people who repeatedly self-harm and to test the cost-effectiveness of this intervention. Currently, there are few tested interventions deliverable in the NHS to support this population.

Particular strengths of the trial are the use of mental health practitioners who would not usually have the opportunity to deliver therapy but whose experience of working with people who self-harm can provide the level of risk management required for safe therapy delivery. Increasing the skills of the existing NHS workforce may increase implementation into clinical practice. At the heart of this study is the experience of people with lived experience of self-harm. This novel intervention and associated research components were designed with significant input from people with lived experience. A diverse panel continue to be a core part of the study team advising on real time changes to the trial as well as participating in the analysis of process evaluation data. This will maximise the intervention uptake and potential effectiveness as well as increasing the impact of dissemination strategies.

The study team have encountered multiple recruitment and implementation challenges which we have been able to address in this protocol to minimise impact on recruitment. There is variation in reported eligible attendances at ED and we know that there may be variability of staffing numbers over any 24 h period which may affect the site’s capacity to recruit.

All clinical teams have reported an increase in staff turnover in the later stages and period post-pandemic. This has been anecdotally attributed to wider NHS workforce retention issues as well as mental and physical stress following the COVID-19 pandemic. These pressures have led to difficulties in sustaining the engagement of the clinical/recruiting team and in communicating the study to ensure staff confidence in introducing the study to potential participants. To address these, additional materials have been developed (patient facing posters, guidance notes for liaison team members, crib sheet for clinicians, reminder cards etc.) as well as additional training to support clinical teams to introduce the study and screen potential participants.

There are also potential challenges in the retention and confidence of trained staff to deliver the intervention, potentially exacerbated by administrative delays to site opening. The trial had planned to train approximately 21 therapists across 12 sites to deliver therapy; however, the retention of trained staff to deliver the intervention in the feasibility suggested this would remain a challenge in the RCT and some sites only having capacity for therapists to take one participant at any one time rather than two. During feasibility, therapists reported a decline in confidence if there was a long gap between training and commencing delivery. Therapists who were less confident reported adhering more closely to the manual and using it as a prompt during sessions. Multiple training sets are planned to train many more therapists than anticipated and to ensure opportunities for brief refresher sessions, and therefore therapist confidence, is maximised.

## Trial status

The trial opened to recruitment in October 2021 and planned to continue for 18 months until March 2023; however, due to multiple recruitment and implementation challenges, a recruitment extension has been granted and recruitment is anticipated to continue for a further 18 months.

As a result of an increased number of therapists trained and delivering the intervention than assumed within our sample size calculation, we anticipate a gain in power and/or a reduction in the number of participants required to maintain a suitably powered trial. We therefore planned to re-estimate the required sample size based on updated clustering assumptions once sufficient data are available on intervention delivery, when 300 participants have been recruited or (as requested by the funder) in October 2023 whichever is sooner. Clustering effects were re-estimated in Autumn 2023 as planned. In February 2024, the funder supported by the Programme Steering Committee agreed a revised recruitment target of a minimum of 348 participants over a total of 36 months. As of 30 June 2024, we had recruited 266 participants across 15 centres. The trial team are still in discussions with new potential centres.

Protocol number and date: 6.0 24 April 2023.

Recruitment started: October 2021.

Anticipated recruitment end: 30 September 2024.

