**Methods:**

FReSH START is a multicentre individually 1:1 randomised controlled trial evaluating the clinical and cost-effectiveness of standard care plus psychological therapy or standard care alone for adults (≥ 18 years) presenting at an emergency department (ED) with repeated self-harm. Recruiting 630 participants, it includes an internal pilot, economic evaluation and process evaluation. The intervention will be delivered by mental health staff working in acute settings, with experience of assessing and managing risk in people presenting to emergency services with self-harm. Staff will be trained and supervised to deliver one of three specially adapted therapies: psychodynamic interpersonal therapy, cognitive behavioural therapy or acceptance and commitment therapy. Participants allocated to the intervention will receive one of the adapted therapies according to therapist allocation for up to 6 months via 12 weekly, one to one, 45–50-min sessions. The primary outcome is quality of life measured by the Clinical Outcomes in Routine Evaluation Outcome Measure at 12 months post-randomisation. Secondary outcomes include suicidal intent, depression and cost-effectiveness. Data are collected using hospital attendance records and online/postal/telephone questionnaires at 6 and 12 months post-randomisation, with resource use additionally collected at 3 and 9 months.

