### Sample size {14}

The recruitment target is 565 participants equally distributed across standard care and intervention plus standard care. This will provide 90% power at 5% significance to detect a between-group difference of three points on CORE-OM (standardised effect size of 0.375) allowing for 25% loss to follow-up and design effect of 1.56. The design effect appropriately inflates the required sample size for an individually randomised controlled trial to account for clustering resulting from therapist-delivered intervention. The design effect assumes (i) cluster size of 11—on average each of 21 intervention therapists treat 15 patients, 11 provide follow-up data; (ii) coefficient of variation of 1.34 to account for variable numbers of patients per therapist (range 3–23) and (iii) intervention intra-cluster correlation coefficient (ICC) of 0.05 [35].

A similar design effect is assumed within the control arm: a wider range of therapists provide treatment as usual, resulting in fewer trial patients per standard care therapist (smaller cluster size) but potentially a higher ICC.

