## Statistical methods

### Statistical methods for primary and secondary outcomes {20a}

A detailed statistical analysis plan will be finalised and agreed by the research team prior to analysis.

A single final analysis is planned after the trial is closed to recruitment and follow-up and when the full database has been cleaned and locked. Analyses will be completed by the CTRU statisticians using SAS version 9.4.

The primary analysis of CORE-OM will use mixed multilevel linear regression with repeated measures (6- and 12-month outcome) adjusted for randomisation stratification factors and baseline value, with therapist treated as a random intercept. Estimated mean treatment differences at each time point will be reported with 95% confidence interval, *p*-values and ICCs. A two-sided 5% significance level will be used for statistical endpoint comparisons, unless otherwise specified.

Secondary outcomes, reliable and clinically significant improvement on the CORE-OM, hopelessness, depression and social connectedness will be analysed using the same approach, i.e. mixed multilevel linear or logistic regression, depending on the type of outcome variable.

Secondary outcomes repetition of self-harm leading to hospital and self-reported repetition of self-harm will be analysed separately.

Cox proportional hazards, accounting for randomisation stratification factors and random therapist effect (multilevel survival frailty model) [40], will be used to test for differences in the time to first repetition and the proportion of participants attending hospital for self-harm at 6 and 12 months. Hazard ratios and corresponding 95% CIs will be presented. If a participant is lost to follow-up, they will be treated as censored. Kaplan–Meier curves will be constructed for each group.

Recurrent event analysis incorporating the timing and cumulative number of hospital attendances for self-harm will be used to test for differences in the rate of recurrent events. Estimated treatment differences will be reported as the hazard ratio with 95% confidence interval and *p*-values.

Self-reported self-harm will be summarised at each follow-up time point (monthly to 12 months).

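### The article's only power figure (90%) belongs to a superseded target of 565. No power is given for the target in force, 348, and lower therapist clustering alone cannot keep 90% at that number.

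*Protocol article*

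**What the plan says.** Three recruitment numbers stand in the protocol article.

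- Abstract, Methods: "Recruiting 630 participants, it includes an internal pilot, economic evaluation and process evaluation".
- Sample size {14}: "The recruitment target is 565 participants equally distributed across standard care and intervention plus standard care". Of this number the section says: "This will provide 90% power at 5% significance to detect a between-group difference of three points on CORE-OM". The inputs are a "standardised effect size of 0.375", 25% loss to follow-up and a design effect of 1.56. The Recruitment section builds its per-site averages on 565.
- Trial status: the funder, supported by the steering committee, "agreed a revised recruitment target of a minimum of 348 participants over a total of 36 months".

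Trial status explains why the number was revisited. More therapists were trained and delivering than the calculation assumed, so "we anticipate a gain in power and/or a reduction in the number of participants required to maintain a suitably powered trial". The size was to be re-estimated on updated clustering assumptions, and the clustering was re-estimated in autumn 2023. The section gives no power, design effect, loss or effect size for 348.

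**The concern.** The article reports a decision of February 2024 and accrual to June 2024, so 348 was already in force when it was written. Yet the Sample size section still states 565 as the current target, and the only power figure in the article is tied to that number. A reader who wants to know what the trial can detect will take 90% for 3 points and apply it to a trial of about 348.

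The stated reason for the cut makes this more than untidy bookkeeping. A lower design effect is a sound reason to reduce a sample size, but only down to the size needed with no clustering at all. If 348 lies below that floor at 90% power, something besides clustering must have changed, and the article does not say what. The practical stake is how a null or borderline primary result is read: the chance of missing a true 3-point difference may be well above the 10% that the article implies.

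**Working it through.** **Inputs.** Difference 3 points and standardised effect 0.375, so SD = 3/0.375 = 8. 90% power, 25% loss and design effect 1.56 (Sample size). Two-sided 5% (Statistical methods). 1:1 allocation (Sequence generation). No baseline correlation is mentioned, so none is credited.

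**Step 1: the plan's own figure.** The normal approximation to the total analysed, with no clustering, is 4 × (1.960 + 1.282)² / 0.375² ≈ 299. The two-sample t calculation gives 300.8, so 301.

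- With the design effect: 300.8 × 1.56 ≈ 469.
- With 25% loss: 469 / 0.75 ≈ 626, or 628 if each arm is first rounded up to 151.

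The stated 565 is therefore not reproduced. It leaves 565 × 0.75 = 423.75 analysed, an effective 423.75 / 1.56 ≈ 272, and power of about 87%. For 565 to give 90%, the design effect would have to be about 1.41. The abstract's 630 does fit the stated inputs (power about 90%).

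**Step 2: the floor with no clustering.** At design effect 1.0, 90% power needs 301 / 0.75 = 401.3, so about 402 randomised. The target of 348 is 54 short of that.

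**Step 3: power at 348.** 348 × 0.75 = 261 analysed. Dividing by the design effect gives the effective size. Power is from the noncentral t distribution. The last column is the difference detectable with 90% power, roughly 8 × 3.242 × √(4 / effective size).

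| Design effect | Effective size | Power for 3 points | Detectable at 90% |
|---|---|---|---|
| 1.00 | 261 | 85.5% | 3.2 points |
| 1.10 | 237 | 82.0% | 3.4 points |
| 1.16 | 225 | 80.0% | 3.5 points |

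To give 90% at 348 the design effect would have to be 261 / 301 = 0.87. Spreading patients over more therapists cannot take it below 1.

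**Step 4: what could reconcile 348.**

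- *80% power.* This needs 225 analysed with no clustering, and 225 × 1.16 / 0.75 = 348 exactly.
- *Baseline correlation r, keeping 90%.* The variance falls by the factor 1 − r², so r must be at least √(1 − 261 / (301 × design effect)). That is 0.36 at design effect 1.0 and 0.46 at 1.10.
- *Lower loss, keeping 90% with no clustering.* Loss could be at most 1 − 301/348 ≈ 13.5%, against the 25% stated in both the Sample size and missing-data sections.

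The article states none of these three.

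**The case against.** The strongest reply is that the article never says 348 gives 90%. That is correct. The 90% is attached to 565, and Trial status promises only a suitably powered trial. A reader might infer that the sponsor made a calculation error at 348, but the text does not support this.

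Nor is 348 arbitrary. It fits 80% power at a design effect of 1.16, and such a design effect is plausible. The fidelity section expects 32 therapists. With 130.5 analysed in the intervention arm that is about 4.1 per therapist, and at the stated ICC of 0.05 with equal clusters the design effect is 1 + 3.1 × 0.05 ≈ 1.15. This is inference, but it shows that lower clustering together with a conventional power level would produce 348.

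The planned primary model also adjusts for baseline CORE-OM and uses both follow-up times, and retention measures were added by amendment. Either could bring power back to 90%. The true power at 348 is therefore undetermined, not shown to be low.

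Two stronger readings should be set aside:

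- Applying the old design effect of 1.56 to 348 gives about 67% power and a detectable difference of about 4.0 points. But 1.56 is the very assumption that was re-estimated because more therapists were delivering.
- Projecting the reported accrual ("As of 30 June 2024, we had recruited 266 participants across 15 centres") forward suggests a final total below 348. That is a forecast, not a fault in the plan: 348 is a minimum and further centres were under discussion.

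Finally, the protocol version cited (6.0, April 2023) predates the revision, so the Sample size section may simply reproduce it. That explains the mismatch but does not remove it, because the same article reports the new target. Details of the re-estimation may properly sit in a later protocol or the SAP. The current target and its power are still needed wherever a target and power are stated.

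**Conclusion.** The point holds as a reporting fault that should be fixed. The target and power in the Sample size section, and the number in the abstract, are not those of the trial being run, and the target in force has no stated power.

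On the article's effect size, two-sided 5% level and 25% loss, with no baseline credit, 348 gives 85.5% power at best and about 80% at a design effect of 1.16. The chance of missing a true 3-point difference is then about 1.5 to 2 times the 10% that readers will assume. The one technical reason given cannot by itself preserve 90%.

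This conclusion depends on those inputs. A baseline correlation of about 0.36 or more, or loss of about 13.5% or less, would restore 90% if there were no clustering. A deliberate move to 80% power would also explain 348. The article does not allow a choice between these.

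Separately, 565 does not follow from its own stated inputs: they need about 626 to 628, and 565 gives about 87%.

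**What to change.** In the Sample size section and the abstract, replace 565 and 630 as current targets with the minimum of 348, and bring the per-site figures in the Recruitment section into line. Alongside 348, state:

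- the power it gives for a 3-point difference, saying plainly if the aim moved from 90% to 80%;
- the re-estimated design effect and its inputs (cluster size, variation in cluster size, ICC);
- any baseline correlation or revised loss to follow-up that was credited;
- the difference detectable with 90% power. Without baseline credit and at 25% loss this is about 3.2 points at a design effect of 1.0 and 3.4 at 1.10.

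If the earlier calculation is kept as history, label it as superseded and correct it: either the target becomes about 626 to 628, or the power stated for 565 becomes about 87%, or the inputs that do give 565 are shown.

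The cost is wording only. No extra participants and no change to the analysis are needed, though the stated power may become less favourable.

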## Data Availability

Data supporting this work are available on reasonable request. Individual participant data (with any relevant supporting material, e.g. data dictionary, protocol, statistical analysis plan) for all trial participants (excluding any participant opt-outs) will be made available for secondary research purposes at the end of the trial, i.e. when all primary and secondary endpoints have been met and all key analyses are complete. Requests to access trial data should be made to [contact] in the first instance. Requests will be reviewed (based on the above principles) by relevant stakeholders, based on the principles of a controlled access approach. No data will be released before an appropriate agreement is in place setting out the conditions of release.

## Abbreviations

AE: Adverse event
ACT: Acceptance and commitment therapy
BHS: Beck Hopelessness Scale
CBT: Cognitive behavioural therapy
CEAC: Cost-effectiveness acceptability curve
CEP: Cost-effectiveness plane
CHEERS: Consolidated Health Economic Evaluation Reporting Standards
CLRN: Comprehensive Local Research Network
CORE-OM: Clinical Outcomes in Routine Evaluation – Outcome Measure
CRF: Case report form
CTRU: Clinical Trials Research Unit
CTS: Cognitive Therapy Scale
DBT: Dialectical behaviour therapy
ED: Emergency department
GCP: Good Clinical Practice
GDPR: General Data Protection Regulation
GP: General practitioner
HRQoL: Health-related quality of life
INHB: Incremental net health benefit
INMB: Incremental net monetary benefit
ICER: Incremental cost-effectiveness ratio
ITT: Intention-to-treat
LIHS: Leeds Institute of Health Sciences
LTHT: Leeds Teaching Hospitals Trust
LYPFT: Leeds and York Partnership NHS Foundation Trust
REC: Research ethics committee
MWtP: Maximum willingness to pay
NHS: National Health Service
NICE: National Institute for Health and Clinical Excellence
NIHR: National Institute for Health Research
NRES: National Research Ethics Service
PIT: Psychodynamic interpersonal therapy
PHQ9: Patient Health Questionnaire 9
PMG: Programme Management Group
PSA: Probabilistic sensitivity analysis
PSC: Programme Steering Committee
QALY: Quality-adjusted life year
REC: Research ethics committee
REDCap: Research Electronic Data Capture
RCSI: Reliable and clinically significant improvement
RCT: Randomised controlled trial
R&D: Research and development
RUSAE: Related, unexpected serious adverse event
SASPD: Standardised Assessment of Severity of Personality Disorder
SAE: Serious adverse event
SC: Standard care
SH: Self-harm
SMS: Short Message Service
SOP: Standard operating procedure
SSA: Site-specific assessment
TMG: Trial Management Group
